# Protocol:

1. Identification of optimal stimulation site for cervical dystonia symptoms: an exploratory study (Version 3.6.14)
2. IRB Review History

N/A

1. Objectives:

I am developing a research program that is centered on the investigation of transcranial magnetic stimulation (TMS) as a diagnostic and therapeutic agent for CD. TMS is an FDA-approved technique that involves generation of a brief magnetic field outside the skull that in turn can excite or inhibit brain tissue, muscle or nerve. In addition, when given repetitively, TMS can induce a temporary increase in inhibition (using low-frequency repetitive TMS (rTMS)) or an increase in excitation (using high-frequency rTMS). These changes can result in therapeutic effects.

The *overall objective* of this application is to target therapeutically the dysfunctional premotor-motor interaction in dystonia—and to provide a focused treatment of specific anatomical networks in order to reduce side effects and to improve symptom control over conventional therapies. We propose using rTMS over distinct premotor areas in patients with CD with the goal of improving symptoms and reducing unwanted side effects.

*Aim 1*: Identify the optimal stimulation site for transcranial magnetic stimulation therapy of symptoms of CD.

Based on our preliminary data, our working hypothesis is that repetitive TMS of a distinct premotor site (e.g. dorsal premotor cortex, ventral premotor cortex, supplementary motor area or anterior cingulate) will provide more effective treatment of CD than non-specific activation of the entire premotor region. Completion of this aim should lead to development of targeted TMS therapy for CD.

It is anticipated that this aim will yield a specific premotor anatomical target to be assessed in a Phase II clinical trial. The future direction is to resubmit the CDMRP grant using key data obtained from this pilot project. The CDMRP grant aims to address the question whether low-frequency rTMS can improve outcomes over those seen with botulinum toxin alone in the treatment of patients with cervical dystonia, specifically by a synergistic effect, to extend the duration of improvement in symptoms.

Successful completion of these studies should lead to rapid adoption of significantly more effective treatment of CD patients. Such results would be valuable for the large population of CD patients, but should also be generalizable to other large populations suffering from other focal dystonias.

1. Background:

After Parkinson disease and essential tremor, dystonia is the third most common movement disorder. It is characterized by abnormal posturing due to sustained muscle contractions, which not only leads to pain but also often causes *significant disability* in activities of daily living such as driving and reading. Primary focal dystonia such as cervical dystonia (CD) affects both genders and all ethnicities and races. The current gold standard treatment of botulinum toxin injections has limitations—painful, frequent injections as well as expected adverse events, which can include dysphagia, neck weakness, voice changes and fatigue. In addition, many CD patients do not have relief of their symptoms for the entire treatment period as the effect “wears off” prior to the next injection. Employment is affected by CD and in one study, a large percentage of patients were not employed even with standard treatment (Skogseid, 2005). *New therapies and new therapeutic targets are urgently needed in this disorder.* Previous work implies that CD is a “neurofunctional” disorder arising from abnormalities of neural connectivity or plasticity, rather than being caused by neurodegeneration. The functional rather than structural nature of the disorder raises the possibility that symptoms of CD can be persistently modified through noninvasive means.

Prior diagnosis and treatment studies have focused on the motor cortex, but our preliminary data suggests that other structures (including premotor cortex) may be more appropriate targets. Our preliminary data revealed abnormal inhibition from the dorsal premotor cortex to the motor cortex in patients with dystonia.

I have previously submitted an application for a clinical trial on rTMS combined with botulinum toxin and CD, supported by the federally funded Congressionally Defined Medical Research Program (CDMRP). The application received positive reviews but additional preliminary data supporting the specific premotor intervention site in CD patients was requested. The present application is designed to obtain this key preliminary data, to allow successful resubmission of the application. This investigation is novel in looking at the important contribution of the premotor cortex to both motor execution and motor planning abnormalities in focal dystonia.

1. Inclusion and Exclusion Criteria

Inclusion:

- Patients with idiopathic cervical dystonia
- Age 18 years or older
- Normal findings in the medical history, physical and neurological examination, except for dystonia
- Last treatment with botulinum toxin more than two months ago

Exclusion:

- History of seizure disorder
- Pregnancy- a pregnancy test will be performed for women of childbearing potential
- Symptoms of a clinically relevant illness in the 4 weeks before the first study day, including history of any other neurological disorders or conditions requiring the use of anti-depressants that are known to increase seizure threshold, neuroleptic medication, anticholinergic drugs and muscle relaxants with the exception of benzodiazepines
- History of neuroleptic medications/ prior use of neuroleptics
- Presence of pacemaker, implanted medical pump, metal plate or metal object in skull or eye

1. Number of Subjects (Recruitment Target)

Fifteen patients with CD meeting the eligibility requirements will be recruited and enrolled.

1. Recruitment Methods

Patients will be recruited from the Botulinum Toxin Clinic at the University of New Mexico Health Sciences Center, referrals from other neurologists that are sent “Dear Dr.” letters, and word of mouth from participants.

1. Study Timelines

Five study days will be scheduled with the patient. The time between study visits should be no less than 2 days (but can be longer than 2 days if necessary) to allow for “wash-out” of any treatment effects prior to the next intervention. The order of the interventions will be randomized. Subjects will be at least 2 months from previous botulinum toxin injection.

All enrollment activities will be concluded by July 1, 2014 with the analysis to be completed by the end of 2015.

1. Study Endpoints

Primary Study Endpoint

- The study will end once recruitment and completion of all study visits achieved.

Secondary Study Endpoint

- The study would end for an individual participant if they desired to withdraw from the study for any reason. We do not anticipate considerable discomfort to the participant during the study sessions, but if a participant found the experimental procedures intolerable, we would immediately stop the study for that participant.

1. Research Setting

For those participants that require an MRI, they will be scanned at the MIND Research Network. The five intervention appointments will all take place in the Noninvasive Neurostimulation Lab located at the CTSC.

1. Study Methods

This study is a randomized, sham-controlled, blinded-rater prospective study—based on the methodology of a successful pilot study in patients with blepharospam (Krantz, 2010). Each participant will receive 15-minute sessions of low-frequency (0.2 Hz) rTMS over the primary motor cortex (MC), dorsal premotor cortex (dPM), supplementary motor area (SMA), anterior cingulate cortex (AC), and a sham condition.

The primary outcome measure will be the change in the Toronto Western Spasmodic Torticollis Rating Scale (TWSTRS) score from baseline to after each of the rTMS interventions, including sham.

The patients will be videotaped and we will send the videos to our collaborator, [name] at NIH, for blinded review of the TWSTRS score. The secondary outcome measures include: measurement of a physiologic marker of inhibition (PMI) pre- and post-intervention, subjective patient rating of symptoms, tolerability rating, and a side effect assessment. The rTMS interventions will be guided by a neuronavigation system (Brainsight™) to ensure consistent placement of coil (Figure 2). Brain MRI will be performed on subjects prior to the first study day for registration in the neuronavigation system.

Incentives: Participants will receive incentives on a graduated pay scale: Days 1-3, $20/day and Days 4-5, $40/day for a total of $140/subject who completed all 5 days plus $20/MRI scan time for a total of $160/subject.

Mileage Reimbursement: We will reimburse at the federal rate of $0.565/mile. The head accountant in the Neurology department will register the participants as vendors on Banner (document attached). This method requires obtaining their social security number, but only the accountant will see this information. The forms will be housed in the neurology department and the study coordinator will have no access to them. The "$600 rule" that is often brought up does not apply to mileage reimbursement as it is paying back money and is not perceived as a "benefit" of participating in the study. Therefore, a participant could theoretically be paid out $601+ for mileage and still not be reported to the IRS. There is a "60 day" rule, however. Any money reimbursed 60 days after the study date would be subject to tax. To avoid this issue, a check will be generated every thirty days, when necessary (although most study participants will be completed within 30 days time).

A paper listing of the link between subject number and identifiable personal information will be kept separate from the main coded dataset and secured in a locked cabinet. This link to the coded information will be kept intact until the end of the study period and in accordance with HRRC and federal requirements for clinical research.

1. List of Appendices

- Dear Dr./Pt letters
- Inclusion/Exclusion Criteria
- Tolerability scoresheet
- Toronto Western Spasmodic Torticollis Rating Scale (TWSTRS)

1. Data and Specimen Banking

- Information and clinical data collected as part of the study will be labeled with participant initials and a study number; information (without the name) will be entered into a computer database/locked file cabinet in the Principal Investigator's office.  The record linking the name to the MRN study ID number (which the MRI scan data is labeled with) will be kept indefinitely at the MRN in a confidential manner in case the participant needs future access to your MRI scan. [name] and her study coordinator will have access to the study information. All other data will be stored for six years and then be destroyed.
- Identification information and data collected from each participant will be entered into the REDCap online data warehouse.
- For each study visit, there will be a neurological exam videotaped both pre- and post-intervention, totaling ten videos. These videos will include identifiable information (i.e. face and voice) and be sent via FedEx 2-day to the NIH collaborator.
- Participation in this study is completely voluntary. Each participant has the right to choose not to participate or to withdraw participation at any point in this study without affecting his/her health care or other services to which they are entitled.

1. Data Management

Data collection and storage

- Information and clinical data collected as part of the study will be labeled with the subject’s initials and a study number, which will be in a locked file cabinet in the locked Principal Investigator’s office; information will also be entered into a secure web-based computer database (REDCap).  The record linking your name to your MRN study ID number (which the MRI scan data is labeled with) will be kept indefinitely at the MRN in a confidential manner in case you need future access to your MRI scan. [name] and her study coordinator will have access to your study information. All other data will be stored for six years and then be destroyed.

Digital recordings

- To participate in this study, agreeing to release the videos taken of the pre- and post-intervention scales is necessary. For each study visit, there will be a neurological exam videotaped both pre- and post-intervention, totaling ten videos. These videos will include identifiable information (i.e. face and voice).
- The videos will be uploaded to a password-protected computer and then deleted off the camera to ensure safety. For the blinded review, the videos will be burned onto a CD. Each file will be encrypted and must have a password to open. This password will be communicated to the collaborators via phone. The CD will be mailed to [name] using FedEx 2day with a required signature for delivery. The CD will be destroyed within one week of being viewed.

a. The password will be different for each CD.

b. We will communicate the password to the NIH collaborator via phone. The collaborator will write it down and destroy it after viewing the videos and completing the rating scales.

c. 7-Zip is a stronger level of security than Ecommerce uses[1] (i.e. Amazon). It is also universal, so it can be used on a MAC or PC interchangeably.

Statistical Plan

- In this exploratory study, the comparison of the primary outcome measure, the TWSTRS score before and after the interventions, and of the secondary outcome measures will be calculated for each intervention separately. The change in scores will be analyzed using repeated measures ANOVA. Locations will be compared with the Tukey adjustment for multiple comparisons. There are no prior data on the influence of rTMS patients with CD, and hence there is not way to calculate a sample size. We have estimated that 7 patients will give us enough information to find out which intervention over which area exerts the largest influence on cervical dystonia.

1. Provisions to Monitor the Data to Ensure the Safety of Subjects

- This study is not considered greater than minimal risk. The PI confers with her mentors on a regular basis in order to review safety precautions and any questions regarding the protocol.

1. Withdrawal of Subjects

- Any subject is free to withdraw from the study at any time.
- The investigator can remove a participant from the study at any time if she believes that by continuing is not in his/her best medical interest, or if he/she is unable to comply with the requirements of the study.

1. Risks to Subjects

- **TMS**: TMS is a safe procedure that has been used on many people to study the brain.  Most people do not find the stimulation painful, but occasionally strong contractions of scalp muscles can cause some discomfort of headache.  If you find the procedure too uncomfortable, you may discontinue it at any time.  Headaches usually go away promptly with nonprescription medication.  The noise of the TMS magnet may affect hearing, so you will be fitted with earplugs to wear during TMS.  Magnetic stimulation will not be performed in people who have pacemakers, implanted pumps or stimulators, or who have metal objects inside the eye or skull.  Please inform the investigators if you have any of these or known hearing loss.  This study employs paired pulse TMS, which is of equivalent safety to previous studies employing paired pulse TMS.  The risk of inducing a seizure with single, or paired-pulse, TMS is considered very low.  Seizures from single/paired-pulse TMS have only been reported in subjects with medically-intractable epilepsy very rarely (0.0-3%).  Safety studies using TMS in patients with neurological disorders have demonstrated no permanence.  Risks to a fetus are not known.  If you think you may be pregnant, you may choose not to participate in this study.
- **EMG**:  There is no risk associated with surface EMG.
- **MRI**: Radio and magnetic waves associated with MRI scans are not associated with any known adverse effects. MRI is non-invasive and considered minimal risk by the FDA. However, the scanner is a large magnet, so it could move objects with iron in them in the room during the scan. This means that loose metal objects, like coin currency or key chains, are not allowed in the MRI room. If you have a piece of metal in your body such as a pacemaker, nerve stimulator, piercings or certain metal surgical implants, you will not be allowed into the MRI room and cannot have an MRI. While in the scanner, you may be bothered by feelings of claustrophobia (fear of small spaces). If you feel uncomfortable (nervous or upset stomach) in the MRI scanner for any reason, tell the research staff. The MRI also makes loud ‘drum’ beating noises during the study. Headphones will be provided for your safety and comfort. There is a speaker in the MRI scan room as well as a window that allows the operator to view you during data collection. This allows the assistants to hear and see you at all times to ensure that you are comfortable and to allow them to respond if you are uncomfortable. You can stop the scan at any time.
- No long-term harmful effects from MRI are known. However, since the effect of MRI on early development of the fetus is unknown, subjects who are pregnant should not go in the MRI. If you are a woman 18 years of age or older and there is a possibility that you may be pregnant, you will be asked to take a urine pregnancy test before being allowed to participate in the study. Rarely, large or recent tattoos can heat up during an MRI scan and cause skin irritation like a sunburn, so the MRI technologist will want to see any tattoos you have prior to the scan.
- There are risks of stress, emotional distress, inconvenience and possible loss of privacy and confidentiality associated with participating in a research study. There may be other risks that are currently unknown. For more information about risks and side effects, ask the investigator.

1. Potential Benefits to Subjects

- There is the possibility of TMS directly improving symptoms related to cervical dystonia, or prolonging the benefit of botulinum toxin injections. This study will also yield generalizable knowledge about the subject’s disorder or condition and thereby improving the risk: benefit ratio in subsequent studies.
- The knowledge gained in this proposed research will identify a specific premotor area to be targeted with rTMS that is expected to result in a novel intervention that could enhance or replace current treatments for CD.  Adjunct treatments to botulinum toxin that could sustain treatment effect and decrease the frequency of re-injection could potentially result in cost savings without a decrease in symptom control. In addition to medical cost reduction, improved quality of life could be expected with the successful development of therapies that extend dystonia symptom control.

1. Vulnerable Populations

- This study is not targeting recruitment from vulnerable populations

1. Multi-Site Research

- This is a single-site study being completed at the University of New Mexico

1. Community-Based Participatory Research/Field Research

- N/A

1. Sharing of Results with Subjects/Incidental Findings

As all participants will be undergoing an MRI before participating in the study, they will receive a report from the MIND within a month after the scan. If there are any incidental findings then the PI will discuss what was found with the participant and offer him/her a copy of the scan on CD to keep in his/her permanent files.

1. Resources Available

The Principal Investigator

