The investigational device has two switches that must be pressed in sequence in order to turn on the device. The device is activated through computer control, which must be accessed through a password-protected computer and knowledge of the Signal software program. Finally, the handheld coils will not discharge unless 2 buttons on either side of the coil are held down simultaneously. The multistep procedure would ensure that an untrained person would be very unlikely to know how to operate the entire setup to cause discharge of the TMS. Again, the device is within a locked laboratory.

Non-Significant Risk Determination Section

- Is the device intended as an implant (≥30 days)?
  - No.
- Is the device for use supporting or sustaining human life?
  - No.
- Is the device for a use of substantial importance in diagnosing, curing, mitigating or treating disease or preventing impairment of human health?
  - No. This protocol is an exploratory study to determine whether rTMS has a beneficial effect on dystonia symptoms to provide preliminary data for a definitive clinical trial.
- Does the use of the device present a potential for serious risk to health, safety or welfare of the subjects?
  - The use of the device does not pose the potential for serious risk to health, safety or welfare of subjects. The protocol parameters are well within the bounds determined by the FDA for approval for the treatment of depression and migraine.

Explain why the use of the device in this study poses non-significant risk, and attach any other supporting information. In addition, explain whether the sponsor, the FDA or any other oversight organization has already made a risk determination for the device.

The device poses a non-significant risk to participants given that the parameters used are well within the FDA-approved rTMS therapy for the treatment of depression. The exclusion and inclusion criteria also ensure an added level of safety in using this device.

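### The antidepressant exclusion names drugs that raise the seizure threshold, which conflicts with the protocol's own seizure-safety purpose

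*Protocol*

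**What the plan says.** The exclusion list in the Protocol, Inclusion and Exclusion Criteria, begins with "History of seizure disorder". A later item excludes clinically relevant illness in the four weeks before the first study day. Within that item it includes a history of other neurological disorders, or "conditions requiring the use of anti-depressants that are known to increase seizure threshold". The same sentence goes on to "neuroleptic medication, anticholinergic drugs and muscle relaxants with the exception of benzodiazepines". A separate item excludes past use of neuroleptics. On the inclusion side the protocol requires "Normal findings in the medical history, physical and neurological examination, except for dystonia".

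Two other places bear on the purpose of these rules. Under Risks to Subjects, the TMS paragraph discusses induced seizure: "The risk of inducing a seizure with single, or paired-pulse, TMS is considered very low". In the Non-Significant Risk Determination Section, after an argument from the stimulation parameters, the protocol adds: "The exclusion and inclusion criteria also ensure an added level of safety in using this device".

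**The concern.** The clause refers to seizure threshold, so its natural reading is as a seizure-safety rule. Its direction does not fit that reading. A screener who applies it as written would look for antidepressants that make seizures harder to provoke, and would find nothing in it about antidepressants with the opposite effect. Because it singles out one subgroup of antidepressants, a screener could also reasonably infer that the others are acceptable.

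Participant safety is at stake, together with the accuracy of a statement in the device-risk justification. No endpoint, sample size or analysis is affected.

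**Working it through.** The protocol gives no figure to reproduce. The check is one of direction, made by setting the passages side by side.

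1. **Meaning of the clause.** The seizure threshold is the level of stimulus needed to provoke a seizure. Threshold up means seizure less likely: named for exclusion by the clause. Threshold down means seizure more likely: not named by the clause.
2. **Against the rest of the list.** The seizure-history item keeps out people at raised seizure risk. The antidepressant clause, taken literally, points the other way.
3. **Against Risks to Subjects.** Induced seizure is a hazard that the protocol itself discusses. The sentence there covers single and paired pulses, and that paragraph gives no corresponding estimate for repetitive stimulation.
4. **Against the device section.** The one purpose stated for the eligibility criteria is added safety in using the device. A clause that refers to seizure threshold but runs in the opposite direction does not contribute to that purpose.
5. **Search for a correction or another reason.** No section of the protocol at hand restates the clause in the other direction or explains why threshold-raising antidepressants should be excluded. The Inclusion/Exclusion Criteria appendix is listed but not available, so its wording is unknown.
6. **What else could catch these patients.** The normal-medical-history inclusion, the clinically-relevant-illness item and the neuroleptic exclusions could each remove some patients on threshold-lowering drugs. None of them mentions antidepressants that lower the threshold.

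For scale only, Study Methods gives 15-minute sessions at 0.2 Hz over four active sites:

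- pulses per session: 0.2 × 15 × 60 = 180
- pulses over four active sessions: 4 × 180 = 720

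These counts describe exposure per participant. They do not measure seizure risk, and nothing in the protocol converts one into the other. The share of candidates taking relevant drugs is not given either.

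**The case against.** The strongest reply is that this is probably a one-word slip with little practical effect. The stimulation rate is low, and the study is described as no more than minimal risk. Staff would understand what was meant, and the broad health criteria would exclude many patients who need antidepressants anyway. It can be added that the clause also lists anticholinergics and muscle relaxants, which the protocol does not link to seizures. A seizure-safety purpose for this particular item is therefore inferred, not stated.

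Much of this stands, and it limits what may be concluded. Three stronger readings are tempting but unsupported:

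- *The protocol admits patients at higher seizure risk.* The clause fails to name them, but the normal-history and relevant-illness criteria may still exclude them.
- *Lower-risk patients are turned away.* The protocol identifies no antidepressant that raises the threshold. If few or none are in use among candidates, the clause excludes nobody.
- *The non-significant-risk determination loses its basis.* That argument rests first on the stimulation parameters, and the criteria are an additional layer. The seizure-history, neuroleptic and implant exclusions operate regardless of this clause, and the protocol also records a determination by the institution's review committee.

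The reply does not remove the inconsistency. Eligibility should not depend on staff reading a criterion as its opposite. A different rationale, such as avoiding drugs that affect the inhibition marker, is conceivable but is nowhere stated.

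**Conclusion.** The clause is wrong as written, or at least unexplained. Its literal direction conflicts with the seizure-history exclusion, with the seizure risk that the protocol discusses, and with the added safety that the device section attributes to the criteria. This rests on the ordinary meaning of seizure threshold and on safety being the only purpose that the document gives for its eligibility rules.

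The size is one clause of one exclusion item, in a study with a recruitment target of fifteen. One part of the safeguard is affected, and other criteria may partly cover the gap. The number of patients concerned cannot be derived from the protocol, and no material harm is demonstrated. The point still merits correction because this is an operative eligibility rule that bears on participant safety.

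**What to change.** The investigator should reconcile the antidepressant clause with the seizure-safety purpose in Risks to Subjects and the Non-Significant Risk Determination Section. If the present wording is deliberate, the protocol should state the reason. Which drugs belong in the criterion is the investigator's clinical decision, and none is proposed here.

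Two checks should follow:

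- Confirm that the Inclusion/Exclusion Criteria appendix and the screening form agree with the reconciled text. The appendix may already be correct.
- Re-check anyone already screened under the current text. Under Confidentiality, the screening records of ineligible candidates are to be destroyed after the project ends, so this should be done while they exist.

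The cost is a wording change in one criterion, a comparison with two other documents and a short re-screen. The design and the analysis are unchanged.

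### Five conditions are given over five sessions with no stated balancing of order and no session factor named in the analysis, so any trend in response over visits would cost precision and make the choice of best site less reliable

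*Protocol*

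**What the plan says.** Under Study Timelines: "Five study days will be scheduled with the patient". The interval between visits "The time between study visits should be no less than 2 days (but can be longer than 2 days if necessary"), which sets a minimum and no maximum. On allocation, the same section says only "The order of the interventions will be randomized". No Latin square, Williams design or other balancing is named.

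Under Study Methods, each participant receives "rTMS over the primary motor cortex (MC), dorsal premotor cortex (dPM), supplementary motor area (SMA), anterior cingulate cortex (AC), and a sham condition", so there are five conditions for five sessions. The primary outcome there is the change in TWSTRS from baseline to after each intervention, and baseline is not tied to a particular visit.

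The Statistical Plan, under Data Management, says "The change in scores will be analyzed using repeated measures ANOVA" and that locations will be compared with a Tukey adjustment. It does not list the factors of the ANOVA and mentions no session, order or carry-over term. It describes the comparison as one of scores before and after the interventions, worked out for each intervention separately. Data and Specimen Banking and Digital recordings both provide for a video before and after the intervention at every visit, ten in all.

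The recruitment target is 15. The Statistical Plan estimates that 7 patients will be enough.

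**The concern.** In a crossover with as many sessions as conditions, session is a second blocking factor beside participant. If it is neither balanced by design nor included in the model, systematic change over sessions goes into the residual. With few participants and simple random order, the conditions also fall unevenly over the sessions, so part of the session trend sits on top of the site contrasts in the one allocation actually used.

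A trend is conceivable here. Participants may respond differently as novelty and expectation fade or as the examination becomes familiar. Carry-over is also possible, since visits may be as little as 2 days apart and the Background section argues that symptoms might be lastly changed by non-invasive means.

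The aim of the study (Objectives, Aim 1) is to rank sites and take one forward to a Phase II trial. A less reliable ranking therefore bears directly on the result the study exists to produce.

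**Working it through.** **No plan figure to reproduce.** The protocol gives no SD, effect size, alpha or power, so its estimate of 7 patients cannot be re-derived. The check below is in units of σ, the within-patient SD of the change score.

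**Inputs.** From the protocol: 5 conditions, 5 sessions, n = 15 (recruitment target) or n = 7 (Statistical Plan). Assumed: simple random order, and a linear trend in the change score of R·σ from session 1 to session 5, with R = 0.5, 1 or 2.

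**Step 1: variance between sessions.** The session means are R × (−0.5, −0.25, 0, 0.25, 0.5). Their sum of squares is 0.625R². Dividing by 4 gives S² = 0.15625R².

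**Step 2: error inflation with no session term.** The factor is 1 + S². The chance shift of one site-versus-site contrast has SD √(2S²/n). The noise SE is √(2/n), which is 0.365 at n = 15 and 0.535 at n = 7.

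| R | Error variance | Shift SD, n = 15 | Shift SD, n = 7 |
|---|---|---|---|
| 0.5 | 1.04 | 0.07 | 0.11 |
| 1 | 1.16 | 0.14 | 0.21 |
| 2 | 1.63 | 0.29 | 0.42 |

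At n = 15 and R = 2 the contrast SE is √(2 × 1.625/15) = 0.47, against 0.365 with no trend. Simulation of 3,000 trials per setting gave inflation of 1.04, 1.14 to 1.16 and 1.62 to 1.64.

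**Step 3: bias and level.** The shift averages zero over randomisations. The simulated type I error of the ANOVA without a session term, under random order, was 4.7 to 5.5% at n = 7 and 4.9 to 5.2% at n = 15.

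**Step 4: unevenness of random order.** The chance that at least one condition is never given first is Σ(−1)^(j+1) C(5,j) ((5−j)/5)^n.
- n = 7: 1.0486 − 0.2799 + 0.0164 − 0.0001 = 0.785.
- n = 15: 0.1759 − 0.0047 + 0.0000 = 0.171.

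This shows imbalance only. It measures neither bias nor variance.

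**Step 5: power of the F test** (one site better by 1σ, 5% level, n = 15).

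| R | Random order, no session term | Random order, session term | Latin squares, session term |
|---|---|---|---|
| 0 | 76% | 73% | 76% |
| 1 | 70% | 73% | 75% |
| 2 | 53% | 72% | 75% |

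At n = 7, adding the session term to a random order changes power from 35% to 30% (R = 0), 32% to 31% (R = 1) and 24% to 31% (R = 2).

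**Step 6: choosing the best condition** (one better by 0.5σ, n = 15). Two separate simulations put the chance of ranking it first, without balancing or session term, at 66% for R = 2, against 76 to 78% with Latin squares and a session term. For R = 1 the figures are 73 to 75% against 78%. With no trend the two are about equal.

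**Step 7: why both changes are needed.**
- A session term with unbalanced order raises contrast variance by about 8% at n = 15 and 22% at n = 7, because site and session are not orthogonal. With Latin squares the rise is about 0% and 3%.
- Latin squares without the session term leave the trend in the error estimate but not in the contrasts. At R = 2 the type I error falls to about 0.6%.

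**The case against.** The strongest objection is that the point rests partly on silence. The Statistical Plan lists no model factors and rules none out, and a separate analysis plan could add a session term. A randomised order is also compatible with drawing sequences from Latin squares. This stands as far as the model goes: a reader might infer that the protocol fixes a location-only ANOVA and an unrestricted order, and it states neither. It does not dispose of the point, because the allocation list is settled before the first visit. A later analysis plan can adjust for an uneven order but cannot recover the 8% (or 22%) of contrast variance lost to it.

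A reader might also infer that site is systematically confounded with session. Step 3 shows otherwise: random order leaves contrasts unbiased on average and the test at its level.

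Botulinum wear-off is a tempting mechanism, because the Background says "many CD patients do not have relief of their symptoms for the entire treatment period" and Study Timelines says "Subjects will be at least 2 months from previous botulinum toxin injection". The first is a general remark on standard care. The Statistical Plan's before-and-after comparison and the paired videos at each visit point to a same-visit baseline, under which additive drift cancels. It would enter in full only if baseline meant the first visit. Study Methods also expects most participants to finish within 30 days.

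Finally, the documents offer no evidence on how large a trend in response might be. That is correct, and the harm is negligible at 0.5σ or below.

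**Conclusion.** The point holds as a low-cost improvement to the design, not as an error that invalidates the analysis. The protocol states neither a balanced order nor a session factor. If responses trend over visits, the loss is in precision and in the reliability of the site ranking: about 4% extra error variance at an assumed trend of 0.5σ, 16% at 1σ and 63% at 2σ. At 15 participants, power in the example falls from 76% with no trend to 70% at 1σ and 53% at 2σ, while the balanced and adjusted design stays near 75%.

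These figures rest on a linear trend in the change score, simple random order and a model without session. The trend size is an assumption in every case. The documents do not support a claim of systematic bias, of an inflated false-positive rate, or of symptom drift contaminating same-visit change scores.

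**What to change.** Make two changes together.

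1. Allocate the 15 participants at random to sequences from three 5x5 Latin squares, for example a Williams pair (10 sequences) plus one further square (5 sequences). Each condition then occurs 15/5 = 3 times in each session.
2. Include session number as a fixed factor in the primary repeated measures model, beside participant and condition.

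State in the same place which score is the baseline. A term for the condition given at the preceding session may be kept as a sensitivity analysis for carry-over. Days since the last botulinum injection should not go into the primary model as well: within a participant it is only elapsed time and is largely collinear with session.

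The cost is a new allocation list and 4 error degrees of freedom. These fall from 14 × 4 = 56 to 52 at n = 15, and the Tukey critical value moves from 3.99 to 4.00. No extra visits or participants are needed, and with no trend essentially no power is lost. At n = 7 the degrees of freedom fall from 6 × 4 = 24 to 20 (4.17 to 4.23), and exact balance over five sessions is impossible. The 7 in the Statistical Plan and the 15 in the recruitment target must therefore be reconciled first. Withdrawals will erode the balance; the session term then still removes the trend, at some loss of precision.
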